### Sample size calculation

G∗power (version 3.1.9.6) is used to calculate the sample size. A total of 16 (8 in the I group and 8 in the C group) patients were included in our preliminary experiments. The number of patients diagnosed with POD was 2 in the I group and 3 in the C group, respectively. On this basis, the calculated sample size that would provide 80% power to detect this difference at a two-sided significance level of 0.05 was 42 patients per group. Considering a dropout rate of 20%, 106 patients will be enrolled in this study.

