### Randomization and blinding

The trial is single-blind because the attending anesthesiologist will collect data and perform PEEP titration without being blinded to the group assignments. Based on a computer-generated randomization sequence performed by an independent investigator, the selected participants will be randomized into Group I and Group C. Envelopes with random numbers will be opened when patients enter the operating room. The allocation ratio is 1:1. Postoperative information collection and the following data analyses will be performed by another researcher who will not participate in this study and know about the grouping allocation.

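### The pilot rates behind the sample size (2/8 vs 3/8) need about 215 patients per group for 80% power; the stated 42 per group gives about 24%

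*Protocol article*

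**What the plan says.** The protocol article's Sample size calculation section gives every input. "A total of 16 (8 in the I group and 8 in the C group) patients were included in our preliminary experiments", and "The number of patients diagnosed with POD was 2 in the I group and 3 in the C group, respectively". It continues that, on the basis of this pilot, "the calculated sample size that would provide 80% power to detect this difference at a two-sided significance level of 0.05 was 42 patients per group". It ends: "Considering a dropout rate of 20%, 106 patients will be enrolled in this study". Randomization and blinding adds "The allocation ratio is 1:1".

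No other event rate, margin or effect size is offered for the calculation. POD within 3 days of surgery is the primary endpoint (Outcome assessment). Statistical methods names Fisher's exact or the chi-squared test for categorical data. The Discussion lists a limited sample size among the limitations but does not revise the power statement.

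**The concern.** The pilot difference is 12.5 percentage points, with both rates in the range where binomial variance is large. Detecting a difference of that size with 80% power usually takes a few hundred patients, so 42 per group looked far too small on sight.

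The 80% figure is the planning claim for the primary endpoint. If true power is near one in four, the trial will probably miss the effect it was designed to find. A reader told that power was 80% could then take a non-significant result as evidence that individualized PEEP does not prevent POD.

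**Working it through.** **Inputs**

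- p_I = 2/8 = 0.25 and p_C = 3/8 = 0.375, so the difference is 0.125 (Sample size calculation)
- Two-sided alpha 0.05, so z = 1.960; power 80%, so z = 0.842 (same section)
- Equal allocation (Randomization and blinding)
- Dropout 20% (Sample size calculation)

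**The part that reproduces.** 42 / 0.8 = 52.5, rounded up to 53 per group, and 53 × 2 = 106. The dropout step is right, so the error lies in the 42.

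**Sample size from the stated inputs**

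Pooled-variance formula, with mean rate p = (0.25 + 0.375)/2 = 0.3125:

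- n = [1.960 × √(2 × 0.3125 × 0.6875) + 0.842 × √(0.25 × 0.75 + 0.375 × 0.625)]² / 0.125²
- n = [1.960 × 0.6555 + 0.842 × 0.6495]² / 0.015625 = 214.7, so 215 per group

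Unpooled formula:

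- n = (1.960 + 0.842)² × (0.1875 + 0.2344) / 0.015625 = 7.849 × 27 = 211.9, so 212 per group

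Arcsine formula, with h = 2·asin√0.375 − 2·asin√0.25 = 0.2709:

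- n = 2 × 7.849 / 0.2709² = 213.9, so 214 per group

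With a continuity correction the pooled figure is 231. Even a one-sided test, contrary to the stated design, would need 167 to 169 (185 with continuity correction). None of these comes near 42, and 215/42 is about 5.1.

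**Power at the planned size, 25% versus 37.5%, two-sided 0.05**

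| Evaluable per group | Normal approximation | Chi-squared, exact enumeration | Fisher's exact, exact enumeration |
|---|---|---|---|
| 42 | 23.2% | 23.7% | 17.4% |
| 53 (no dropout) | 28.2% | 29.1% | 21.8% |

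Exact enumeration sums the binomial probabilities of every pair of event counts that the test declares significant.

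**What 42 per group can detect.** With control at 37.5%, chi-squared power is 80.1% when the group I rate is 12%. Fisher's test has 77.5% power at 11% and 81.7% at 10%. The required fall is 37.5 − 12 = 25.5 points, about twice the pilot difference.

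**Precision.** The 95% CI half-width for the risk difference is 1.96 × √(0.4219/n). That is 19.6 points at n = 42 and 17.5 points at n = 53. Both exceed the 12.5-point design difference.

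**How firm the pilot rates are.** The groups differ by one event among 16 patients (Fisher p = 1.0). The exact 95% CIs are 3.2% to 65.1% for 2/8 and 8.5% to 75.5% for 3/8.

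**The case against.** The article condenses a fuller protocol, which might rest the calculation on other rates. That does not help here. The article prints the inputs and the output together and ties the second to the first, so they contradict each other whatever another document says.

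The sample size is already conceded to be limited. The Discussion does say so, but a general limitation does not withdraw a specific claim of 80% power.

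Four narrower points stand:

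- The 24% is conditional. It assumes 42 evaluable per group, the chi-squared test and the pilot rates. Across the two named tests and zero to 20% dropout, the range is about 17% to 29%.
- Only standard two-proportion formulas were tried. How the 42 arose cannot be established from the article.
- Statistical methods also plans a stratified Mantel–Haenszel comparison of POD. Its strata are not fully specified, so its power was not computed. In my judgement stratification would not make up a five-fold shortfall.
- The pilot is too small to establish a control rate, so the 12% threshold is also conditional on 37.5%.

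None of these brings the stated figure within reach of 80%.

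**Conclusion.** The statement is wrong as written and must be corrected. The protocol's own inputs require about 215 evaluable patients per group. At the planned 42, power is about 24% by chi-squared test (17% by Fisher), so if the assumed effect were real the trial would miss it roughly three times in four. The enrolment target of 106 inherits the error, although the dropout step is sound.

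The conclusion rests on the stated rates, the two-sided 0.05 level and 1:1 allocation. It does not depend on the choice among standard formulas or between the two tests named. Confidence is high.

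**What to change.** Correct the Sample size calculation section as follows:

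- Remove the claim that 42 per group gives 80% power for the pilot difference.
- State that 106 enrolled (about 84 evaluable) gives about 24% power by chi-squared test, or 17% by Fisher, for 25% versus 37.5%. Say that these rates come from 8 patients per group.
- State that, with control at 37.5%, 80% power is reached only if the group I rate is about 12% (about 10% with Fisher).
- Describe the POD comparison as an estimate, reported as a risk difference with its 95% CI, and say that a non-significant result cannot be read as no effect.

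This costs protocol wording only. The stated power becomes less favourable and no extra patients are needed.

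If the sponsor wants to keep 80% power for the 12.5-point difference, the size has to change: 215 / 0.8 = 268.75, so 269 per group and 538 in total. Trial status reports only 12 participants recruited at submission, so re-planning could be considered at that stage. It would be a much larger undertaking and would need ethics review as a protocol amendment. Powering for a larger difference instead would need a justification that the pilot does not supply.

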### Statistical methods

SPSS (version 22.0, IBM) will be used for statistical analyses. The data with a normal distribution are expressed as mean ± standard deviation (SD) and compared by independent-samples t tests. The data of non-normally distribution are expressed as median (interquartile range) and compared by Mann-Whitney U-tests. Categorical data are described as numbers or percentages and analyzed using Fisher’s exact test or chi-squared test. Univariate repeated measures ANOVA will be used for intra-group comparisons and post hoc tests with Bonferroni correction will be used to control for Type I error. We will perform a Mantel–Haenszel test, stratified according to whether MAP < 55 mmHg occurs during PEEP titration and other possible confounding factors, to compare the risks of POD in each group. *P* values < 0.05 will be considered statistically significant.

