### Outcome assessment

The primary endpoint of this trial will be the incidence of POD within 3 days after surgery. POD will be determined by an independent researcher who will not know the group assignment using CAM [17]. The investigator will participate in a training session including symptoms and diagnosis of delirium and will not know the group assignment. The researcher will assess POD once daily, between 6: 00 am to 8: 00 am. Four key delirium characteristics consist of CAM diagnostic criteria: (1) acute onset and disease fluctuations, (2) inattention, (3) changes in consciousness, and (4) disordered thinking. Delirium will be defined as the presence of (1) and (2), accompanied by (3) or (4) or both [7].

The secondary outcomes will include perioperative rSO_2_ measurement, arterial blood gases, respiratory variables, and plasma concentrations of interleukin (IL)-1β, IL-6, and NSE. The baseline rSO_2_ will be obtained within 2 minutes before anesthesia induction and averaged. Additionally, intraoperative rSO_2_ values will be continuously measured and recorded using a cerebral oximeter at the following timepoint: T_0_: after entering the operating room; T_1_: 5 minutes after starting mechanical ventilation in the supine position; T_2_: 60 minutes after turning over; and T_3_: 5 minutes after taking in the supine position. The serum concentrations of interleukin (IL)-1β, IL-6, and NSE will be determined by ELISA kits. We will collect the blood samples 15 minutes before anesthesia induction (T_0_) and postoperative day 1.

Arterial blood gases will be measured at T_1_ to T_4_ (after breathing air in PACU for 20 minutes). Respiratory variables including P_ET_CO_2_, PEEP, P_peak_, mean airway pressure (P_mean_), Cdyn, PaO_2_/FiO_2_, A-aDO_2_, V_D_/V_T,_ and Qs/Qt will be recorded at T_1_ to T_3_. Each patient will receive two ultrasound examinations at T_1_ and T_4_. And lung ultrasound scans will be performed by an experienced anesthetist who will not know the group allocations. As described previously [18, 19], each hemithorax will be alienated into 6 quadrants and each region will be assigned a score of 0 to 3 according to the different signs of B-line, subpleural consolidation and pleural line under ultrasound scan. The LUS will be calculated to quantitatively assess the aeration loss by adding all scores up.

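### Repeated secondary outcomes: the only repeated-measures analysis is within arms, and the between-arm tests leave the collected baseline values unused, at a cost in precision

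*Protocol article*

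**What the plan says.** All of the following is in the protocol article.

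**Statistical methods**
- Within arms: "Univariate repeated measures ANOVA will be used for intra-group comparisons". The same sentence adds that "post hoc tests with Bonferroni correction will be used to control for Type I error".
- Between arms, normally distributed data are "compared by independent-samples t tests" and other continuous data are "compared by Mann-Whitney U-tests". No covariate is named.
- The one stratified analysis, a Mantel–Haenszel test, is there "to compare the risks of POD in each group". It concerns the binary primary endpoint only.

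**Outcome assessment**
- rSO2 has a pre-induction baseline and is recorded at T0, T1, T2 and T3.
- For IL-1β, IL-6 and NSE: "We will collect the blood samples 15 minutes before anesthesia induction (T_0_) and postoperative day 1".
- Respiratory variables are recorded at T1 to T3 and blood gases at T1 to T4.
- For lung ultrasound: "Each patient will receive two ultrasound examinations at T_1_ and T_4".

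**Interventions**
- Both arms have PEEP 5 cm H2O after intubation. Titration in group I starts only once the patient is prone. T1 is 5 minutes after the start of ventilation, still supine, so it comes before the arms diverge.

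**The concern.** The Background states that individualized PEEP should prevent delirium by lowering inflammation and raising rSO2. The repeated secondary outcomes are the trial's evidence on that mechanism, so the question they must answer is whether the arms differ after titration.

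The stated repeated-measures analysis answers another question, namely whether values change over time inside each arm. rSO2 or IL-6 can move in both arms because of anaesthesia, positioning or surgery. The between-arm tests do address the right question, but one time at a time and without the pre-intervention value. No analysis uses T2 and T3 together to compare the arms. In a trial whose Discussion calls its own sample size limited, information already paid for goes unused.

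**Working it through.** **Plan's own figure.** The article gives no SD, effect size, correlation or power for any secondary outcome, so there is nothing to reproduce for them. The only sample size is for the primary endpoint: 42 per group, then 42/0.8 = 52.5, rounded to 53 per group and 106 in total. That dropout step reproduces. The 42 itself does not follow from the quoted pilot rates: 3/8 against 2/8 at two-sided 0.05 and 80% power needs about 215 per group. That is a separate matter. Here 42 serves only as the number per arm the plan expects to analyse.

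**Step 1: which outcomes have a usable baseline.**

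| Outcome | Before the arms diverge | After |
|---|---|---|
| rSO2 | pre-induction baseline, T0, T1 | T2, T3 |
| IL-1β, IL-6, NSE | T0 | postoperative day 1 |
| Respiratory variables | T1 | T2, T3 |
| Blood gases | T1 | T2, T3, T4 |
| Lung ultrasound score | T1 | T4 |
| VAS | none described | postoperative |

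PEEP is listed among the respiratory variables, but it is 5 cm H2O in every patient at T1. A constant cannot serve as a covariate.

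**Step 2: variance after adjustment.** Let r be the correlation between baseline and follow-up (assumed). ANCOVA multiplies the residual variance by 1 − r², and 42 per arm act like 42/(1 − r²):
- r = 0.3: 1 − 0.09 = 0.91; 42/0.91 ≈ 46
- r = 0.5: 1 − 0.25 = 0.75; 42/0.75 = 56
- r = 0.7: 1 − 0.49 = 0.51; 42/0.51 ≈ 82

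**Step 3: detectable difference and power.** At two-sided 0.05 and 80% power, the detectable difference in SD units is (1.96 + 0.84) × √(2/42) = 0.61 unadjusted. Multiplying by √(1 − r²) gives the adjusted value. Power is for an assumed true difference of 0.5 SD (normal approximation).

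| Analysis | Detectable difference | Power at 0.5 SD |
|---|---|---|
| Unadjusted t test | 0.61 SD | 63% |
| ANCOVA, r = 0.3 | 0.58 SD | 67% |
| ANCOVA, r = 0.5 | 0.53 SD | 75% |
| ANCOVA, r = 0.7 | 0.44 SD | 89% |

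**Step 4: simulation check** (5,000 trials per scenario, 42 per arm, normal data). With no treatment effect, the t test rejected in 4.7% to 5.3% of trials and ANCOVA in 4.9% to 5.3%. Both hold their level. With a 0.5 SD effect, the t test had 61% to 62% power, and ANCOVA had 65%, 73% and 88% at r = 0.3, 0.5 and 0.7. The difference between the methods is precision, not validity.

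**The case against.** The strongest defence is that the plan does test the treatment effect. Allocation is randomised 1:1, and an unadjusted comparison at a post-intervention time is unbiased and holds its type I error. Chance baseline imbalance is already covered by its standard error. This stands. It applies most clearly to the biomarkers and lung ultrasound score, which have one follow-up value and hence no trajectory to model.

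Three stronger readings are tempting, and the documents do not support them.

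- A reader might infer that a treatment effect will be claimed when one arm changes significantly and the other does not. That would be unsound: if two identical arms each have within-arm power p, they disagree with probability 2p(1 − p), at most 50% (at p = 0.5). But the article nowhere says it will reason this way, and it lists between-arm tests alongside.
- A reader might infer that every repeated outcome can be baseline-adjusted. PEEP and VAS cannot.
- A reader might infer that the Bonferroni correction belongs on the between-arm contrasts instead. Two or three independent tests at 0.05 do carry 9.8% to 14.3% family-wise error, and less if positively correlated. For secondary outcomes, however, correcting them is a trade-off and not an error to be put right.

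It is also fair to say that the gain rests on an unknown r. T0 values are taken before anaesthesia and set against values under prone anaesthesia or on the day after surgery, and T4 blood gases are taken on room air. A low r cannot be excluded, and at 0.3 the gain is small.

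Finally, a condensed article may leave model details to a fuller document. That does not remove the point: the article does name its methods, and it expressly assigns the repeated-measures one to within-arm comparisons.

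**Conclusion.** The point holds as one of precision and of a missing analysis, not of bias. The stated repeated-measures ANOVA cannot show a difference between arms. The stated between-arm tests can, validly, but they omit baseline values the schedule provides and do not compare the arms across T2 and T3 (and T4 for blood gases).

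The variance reduction forgone is 9%, 25% or 49% at r = 0.3, 0.5 or 0.7. These figures rest on an assumed r, on 42 analysed per arm, and on a roughly linear relation between baseline and follow-up. For outcomes that would go to the Mann-Whitney test they are only a guide. The point concerns secondary outcomes; the analysis of delirium is not touched.

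**What to change.** In Statistical methods, replace the analysis of the repeated secondary outcomes as follows.

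- **rSO2, blood gases, and respiratory variables other than PEEP:** a linear mixed model with group, time, group-by-time and the pre-intervention value as covariate. Name one baseline for rSO2 in advance, since several are recorded; use T1 for the others. Report the between-group difference with 95% CI at T2 and T3, and at T4 for blood gases.
- **IL-6, IL-1β and NSE:** ANCOVA on the day 1 value adjusted for T0, on the log scale if skewed.
- **Lung ultrasound score:** ANCOVA on the T4 value adjusted for T1.
- **Within-group changes:** descriptive only, with a sentence saying they will not be used to infer a treatment effect.
- **PEEP and VAS:** left out of the baseline adjustment.

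The cost is analysis wording. No measurement, visit or patient is added, and both models can be fitted in SPSS. The change should go through the ethics committee as the Protocol amendments section requires, and be fixed before outcome data are compared by group. The Trial status section reports 12 participants recruited at submission.

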The patients in both groups will receive the PEEP of 5 cm H_2_O after endotracheal intubation, and this PEEP level will be maintained throughout the whole procedure in the group C. After the prone position is set up, patients in Group I will receive optimal individualized PEEP identified by an incremental PEEP titration protocol (Fig. 2). The PEEP titration method is as follows: each PEEP level (4, 6, 8, 10, 12, 14, 16 cm H_2_O) will be maintained for 60 s. Meanwhile, we will record the Cdyn at each PEEP level. We will select the optimal PEEP level based on the maximum Cdyn and maintain it throughout the whole study period. If circulatory instability occurs during PEEP titration, intravenous infusion of noradrenaline will be used to maintain MAP ≥ 55mmHg.

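### The Mantel-Haenszel test of POD is stratified on an event that follows randomisation and can arise only in Group I, so it drops those Group I patients and can bias the comparison

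*Protocol article*

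**What the plan says.** Four parts of the protocol article bear on this.

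- **Outcome assessment:** "The primary endpoint of this trial will be the incidence of POD within 3 days after surgery".
- **Randomization and blinding:** allocation is revealed before anaesthesia. "Envelopes with random numbers will be opened when patients enter the operating room".
- **Interventions:** "After the prone position is set up, patients in Group I will receive optimal individualized PEEP identified by an incremental PEEP titration protocol". Group C starts at 5 cm H2O and "this PEEP level will be maintained throughout the whole procedure in the group C". The 55 mmHg threshold is itself tied to the titration step: "If circulatory instability occurs during PEEP titration, intravenous infusion of noradrenaline will be used to maintain MAP ≥ 55mmHg".
- **Statistical methods:** a Mantel-Haenszel test will be done "to compare the risks of POD in each group", "stratified according to whether MAP < 55 mmHg occurs during PEEP titration and other possible confounding factors". The same section assigns categorical data in general to Fisher's exact or the chi-squared test. It does not say which of these tests governs POD.

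**The concern.** A stratification factor in a randomised comparison should be fixed before allocation and able to take each of its values in either arm. This one meets neither condition. It is observed during a step that comes after allocation and that only one arm undergoes. The plan treats it as a confounder, but an event that follows allocation and belongs to the procedure under test cannot confound the randomised comparison. It is a possible consequence of the intervention.

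What is at stake is the comparison on the primary endpoint. If the stratified test supplied the reported result, Group I would be judged without its patients who had low pressure during titration, while the Group C patients who resemble them would all stay in.

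**Working it through.** **1. When and where the stratifier can occur**

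| Step | Group I | Group C |
|---|---|---|
| Entry to operating room | envelope opened | envelope opened |
| After intubation | PEEP 5 cm H2O | PEEP 5 cm H2O |
| After turning prone | titration, 4 to 16 cm H2O | stays at 5, no titration |
| MAP < 55 mmHg during titration | yes or no | cannot be yes |

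**2. What a stratum without controls contributes**

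In stratum k, let a be the POD cases among n_I patients in Group I, c the cases among n_C in Group C, m = a + c and N = n_I + n_C.

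- Risk ratio: sum of a·n_C/N divided by sum of c·n_I/N.
- Test: sum of a − n_I·m/N, with variance n_I·n_C·m·(N − m)/(N²(N − 1)).

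With n_C = 0 we have c = 0, m = a and n_I = N. Both risk-ratio terms are 0, observed minus expected is a − a = 0, and the variance is 0. The stratum drops out of both the estimate and the test.

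**3. Worked example (invented counts)**

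Group I has 14/42 with POD (hypotensive 6/12, others 8/30) and Group C has 14/42.

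- Crude risk ratio: (14/42)/(14/42) = 1.00.
- Stratified: (8 × 42/72)/(14 × 30/72) = 4.667/5.833 = 0.80.
- Test: 8 − 30 × 22/72 = −1.167, variance 3.766, z = −0.60.

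Deleting the 12 hypotensive Group I patients gives exactly the same figures.

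**4. Size under assumed rates**

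The protocol disputes or states no figure on this point, so there is nothing of its own to reproduce except the arm size: 42 per group, and 42/0.8 = 52.5, rounded to 53, gives 106. I use 42 as the planned evaluable number; how it was derived is a separate matter. The protocol gives neither the frequency f of MAP < 55 mmHg nor the POD risk in such patients, so both are assumptions.

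Set POD at 30% in both arms, so that assignment has zero net effect, and at 50% among hypotensive Group I patients. The risk in the remaining Group I patients is (0.30 − 0.50f)/(1 − f). The spurious difference is that risk minus 0.30. Type I error is simulated, two-sided 0.05, without continuity correction.

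| f | Risk in retained Group I | Spurious difference | Type I error, stratified |
|---|---|---|---|
| 2% | 0.290/0.98 = 29.6% | −0.4 points | about 5.0% |
| 5% | 0.275/0.95 = 28.9% | −1.1 points | about 5.1% |
| 10% | 0.250/0.90 = 27.8% | −2.2 points | about 5.4% |
| 20% | 0.200/0.80 = 25.0% | −5.0 points | about 7.5% |
| 30% | 0.150/0.70 = 21.4% | −8.6 points | about 12.2% |

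The unstratified test stays at about 5% in every row. Because the 50% is held fixed, the ratio of risks also rises down the table, from 50/29.6 = 1.7 to 50/21.4 = 2.3. The growth is therefore not due to frequency alone.

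**5. Direction**

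Now hold the risk ratio r (hypotensive to non-hypotensive) fixed, again with equal overall risk in the two arms. The expected stratified risk ratio is 1/(1 − f + f·r). At f = 20%:

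- r = 2: 1/1.20 = 0.83, favouring Group I.
- r = 1: 1.00, no bias.
- r = 0.67: 1/0.934 = 1.07, favouring Group C.

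**The case against.** A reader might infer that the plan does bias the trial toward individualized PEEP. The documents do not support that as a fact. It needs a higher POD risk in hypotensive patients, and no such rate is given. The Discussion links reduced brain perfusion and lower rSO2 to POD, but as a mechanism, and in connection with turning prone rather than with brief pressure drops during titration. The direction must stay conditional.

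A reader might also infer that the primary endpoint has no sound analysis. That goes too far. POD is categorical, and Fisher's exact or the chi-squared test is named for such data, so the Mantel-Haenszel test may be meant as supplementary. What stands is that the section does not say which test governs, and that the only test naming POD is the faulty one.

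The event may be uncommon. Titration is seven steps of 60 seconds, vasoactive drugs are planned, and noradrenaline is planned for instability. At 2% to 5% the distortion is about one point or less, and the error rate barely moves. That limits the likely size but does not make the stratifier valid.

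If hypotension truly causes POD, equal overall risk in the two arms implies an offsetting benefit in the other Group I patients. The differences in the table are then departures from the net effect of assignment, not proof that no patient benefits. Nor do the documents show that the dropped patients were harmed.

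Finally, pressure in Group C could be recorded over a matched period. The protocol does not say so, and the analysis would still condition on something the intervention can change. The unnamed further factors are detail that a SAP may supply; the point does not rest on them.

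**Conclusion.** Wrong as written. From the document alone it is certain that the stratifier follows allocation, that it can occur only in Group I as the procedure is described, and that its positive stratum has zero Mantel-Haenszel weight. The test therefore sets non-hypotensive Group I patients against all of Group C.

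The consequence is conditional. If hypotensive patients carry a higher POD risk, the result leans toward individualized PEEP; with equal risk only patients are lost; with lower risk the lean reverses. Under the assumed rates the distortion ranges from negligible (−0.4 points) to serious (−8.6 points, error about 12.2%). Nothing in the protocol locates the trial within that range.

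**What to change.** In Statistical methods:

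1. Delete MAP < 55 mmHg during titration as a stratification factor.
2. State that the primary analysis of POD is the unstratified between-group comparison (chi-squared or Fisher's exact), by randomised group and without excluding patients for titration hypotension.
3. If a Mantel-Haenszel test is kept, stratify only on baseline factors specified in advance.
4. Report titration hypotension descriptively as a Group I safety result, in line with the Safety evaluation section, which already lists hypotension as an adverse event.

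The cost is a sentence or two and the ethics committee review that any protocol change receives. No extra patients are needed, and no measurement beyond those planned. How to handle patients who meet the Discharge criteria is a separate question that this change does not settle. Since 12 participants had been recruited at submission, the change should be made before any comparison by group.
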